## Abstract

**Background:**

Fever is a common symptom in the emergency department(ED). Fever can be caused by bacterial infections, which are treated with antibiotics. Often, bacterial infections cannot be ruled out in the ED using standard diagnostics, and empiric antibiotic treatment is started. Procalcitonin(PCT) is a biomarker for bacterial infections, but its role in an undifferentiated ED population remains unclear. We hypothesize that PCT-guided therapy may reduce antibiotics prescription in undifferentiated febrile ED patients. The primary objectives of this study are to determine a) the efficacy, b) the safety of PCT-guided therapy, and c) the accuracy of the biomarker PCT for bacterial infections. The secondary objective is to study the cost-effectiveness of PCT-guided therapy.

**Methods/design:**

This is a multicenter noninferiority randomized controlled trial. All adult ED patients with fever(≥38.2 °C) are randomized between standard care with and without the addition of a PCT level, after written informed consent.For efficacy, the reduction of patients receiving antibiotics is calculated, using a superiority analysis: differences between the PCT-guided group and control group are assessed using a Fisher’s exact test, and a multivariable logistic regression analysis to account for the effects of demographic and medical variables on the percentage of febrile patients receiving antibiotics.Safety consists of a composite endpoint, defined as mortality, intensive care admission and ED return visit within 14 days. Noninferiority of PCT will be tested using a one-sided 95 % confidence interval for the difference in the composite safety endpoint between the PCT-guided and control groups using a noninferiority margin of 7.5 %.Accuracy of PCT and CRP for the diagnosis of bacterial infections will be reported, using the sensitivity, specificity, and the area under the receiver-operating-characteristic curve in the definitive diagnosis of bacterial infections.

The sample size is 550 patients, which was calculated using a power analysis for all primary objectives. Enrollment of patients started in August 2014 and will last 2 years.

**Discussion:**

PCT may offer a more tailor-made treatment to the individual ED patient with fever. Prospective costs analyses will reveal the economic consequences of implementing PCT-guided therapy in the ED.

**This trial is registered in the Dutch trial register:**

NTR4949

## Background

Fever is one of the most common symptoms of patients visiting the emergency department (ED). The etiology of fever is diverse, ranging from infectious diseases to neoplasms and trauma [1]. Specific etiologies of fever, such as severe bacterial infections, have to be treated within one hour after ED presentation with adequate antibiotic therapy, according to the surviving sepsis guidelines [2].

Because time is of the essence in the initiation of therapy, physicians in the ED have a limited time window for diagnosing the etiology of fever. This results in a “better safe than sorry” approach, in which broad-spectrum antibiotics are administered to febrile patients, only based on history and physical examination, and readily available diagnostic entities.

On the other hand, antibiotic resistance is becoming an increasing problem worldwide. Antimicrobial stewardship advocates thoughtful initiation of antibiotic therapy. Thus, in treatment of bacterial infections, both under-treatment and overtreatment are undesirable. Therefore, it is vital to increase the accuracy of diagnostics of febrile illness.

The mainstay of diagnosing the etiology of fever in the ED consists of history, physical examination and laboratory analysis of serum and other bodily fluids, and chest X-ray examinations. Cultures and viral throat swabs are obtained, but are of no use in the ED, because results take several hours to days and treatment has to be started early after ED presentation [2]. Currently, leukocyte count, with or without leukocyte differentiation, and C-reactive protein (CRP) are the laboratory discriminators of choice in the initial approach in the diagnostic process of febrile diseases.

A higher accuracy of ruling in or ruling out bacterial infections using biomarkers may result in more accurate antimicrobial therapy. On the individual patient level, fewer patients would be treated empirically with antibiotics. Adverse events and drug interactions would be reduced. Also, a more accurate diagnosis could save hospital expenses and result in cost reductions. On a population level, antibiotics resistance could be countered. For patient safety, this should obviously be without an added risk of under-treatment.

Procalcitonin (PCT) is a promising biomarker for bacterial infections. PCT is a precursor protein of calcitonin. Unlike calcitonin, which is only produced in the C-cells of the thyroid gland, PCT can be produced ubiquitously throughout the human body. The production of PCT is upregulated by proinflammatory cytokines like interleukin -1 (IL-1), IL-2, IL-6 and tumor necrosis factor alpha, and directly by bacterial endotoxins and lipopolysaccharide. Interferon gamma, a cytokine associated with viral infections, reduces the upregulation of PCT. It has been shown that PCT levels in non-infectious febrile conditions, such as autoimmune diseases or fever caused by malignant disorders stay low, whereas CRP levels often rise significantly [3]. Furthermore, an increase in PCT levels can be monitored within 4 to 6 h after start of infection [4–6]. In comparison, CRP is an acute phase protein synthesized exclusively in the liver. CRP levels increase during inflammatory states, but are not specific for bacterial infections and take more time, 6 to 48 h after start of infection, to be detectable compared to PCT [5, 7]. These characteristics give PCT a theoretical advantage over CRP.

Recently, clinical studies have focused on PCT as a biomarker of bacterial infections, showing better diagnostic properties than commonly used markers such as CRP [3, 8–14]. Studies have shown that PCT-guided antibiotic therapy- i.e. starting or withholding antibiotics, based on the PCT-level - is safe and reduces prescription of antibiotics in several distinct patient groups: savings of more than 23 % in the intensive care unit (ICU) and up to 78 % in the general practice setting [8, 11, 15]. However, evidence of the effectiveness of PCT-guided antibiotic therapy in an undifferentiated ED population is scarce.

The ED is the gateway of hospital healthcare. Patients enter with symptoms and leave with a diagnosis. Either they are admitted, or are sent home. For almost every diagnosis, there are numerous medical tests and interventions available that can be utilized in the ED. However, budgets are limited and should therefore be used in the most efficient manner possible. ED based cost-effectiveness studies are used to estimate the value for money offered by new technologies. These studies serve as a tool for hospital administrators and decision makers who are responsible for prioritizing interventions under economic constraints [16].

Estimated yearly costs associated with antibiotic resistance in Europe are in the range of 1.5 billion euros, comprising extra healthcare costs and productivity losses caused by infections due to antibiotic-resistant bacteria [17]. PCT-guided therapy may contribute to a reduction of these enormous costs. It may lead to a reduction in costs of antibiotics and additional diagnostics tests, such as blood cultures in non-bacterial disease. Costs of hospital admissions could be reduced as admission for observation may become obsolete. As an added effect, there may be a reduction of productivity losses, related to paid and unpaid work. Patients may be able to return to their daily activities faster.

The current evidence on the cost-effectiveness of PCT-guided therapy consists of retrospective hypothetical models. One study analyzed the cost-effectiveness of PCT testing in patients hospitalized for community-acquired pneumonia with a mathematical model [18]. The authors showed that a PCT-guided protocol would cost less and would be more effective than usual care [18]. Recently, a model-based study from the US assessed the economic impact of PCT testing in patients with acute respiratory tract infections. The authors documented that PCT-guided care was cost saving in inpatient, ICU and outpatient settings, mainly due to a reduction in antibiotic costs. Total yearly savings at the US national level were calculated at 1.6 billion dollars [19].

These estimates only included costs of PCT testing and savings on costs of hospitalization, excluding savings from other care consumption and productivity losses, which cannot be estimated at this stage. There is a need to broaden the evidence base to promote the efficient use of PCT-guided therapy in patients with fever presenting at EDs.

The primary objectives of this study are to determine a) the efficacy and b) the safety of PCT-guided therapy, and c) the accuracy of the biomarker PCT for bacterial infections. The secondary objective is to study the cost-effectiveness of PCT-guided therapy.

## Methods and design

The HiTEMP study is designed as a multicenter noninferiority randomized controlled trial on PCT-guided therapy. The study will be performed in both academic and non-academic teaching hospital settings. Patients will be asked for written informed consent. Patients who consent are randomized using an online computer program, to either the standard-of-care diagnostic workup of febrile patients (control group), or the standard-of-care workup with the addition of the diagnostic biomarker PCT.

### Outcome measures

#### Primary outcome measures

The efficacy of PCT-guided therapy is defined as the percentage of patients who are prescribed antibiotics in the ED.The safety outcome measure consists of a composite endpoint of 30 days mortality, intensive care unit (ICU) admission within 30 days, or a return visit to the ED within 14 days.The accuracy of the definitive diagnosis is reported for PCT and CRP using the sensitivity, specificity, and the AUC of the diagnosis of bacterial infections. The definitive diagnosis is defined in two ways. 1. As “confirmed bacterial infection”, in which culture – and PCR results that fit the clinical case presentation are used to report presence of bacterial infections. 2. As “suspected bacterial infection”, in which two independent physicians will give their expert opinion on the presence of a bacterial infection using culture results, image modalities and clinical course, in case of discrepancy, a third physician will decide.

### Secondary outcome measures

Secondary outcome measures for cost-effectiveness are hospital treatment costs, related medical consumption during follow-up, costs of absenteeism and reduced productivity while at work.

The adherence to PCT advice is reported, including the percentage of antibiotic prescriptions with low PCT result, and withholding of antibiotics in patients with high PCT result.

The percentage of patients who received antibiotics without suspected bacterial infection is reported.

Outcome measures are reported for the total patient population, and are stratified by source of infection: respiratory tract infections, urinary tract infections, skin and soft tissue infections, central nervous system infections, abdominal infections, non-infectious fever, fever without source, and other causes of fever.

### Inclusion and exclusion criteria

Inclusion criteria: All patients of 18 years and older visiting the ED, with a temperature of ≥ 38.2 °C (100.8 °F) are eligible. Temperature is measured using an ear thermometer, in triage. Eligible patients need to provide written informed consent.

Exclusion criteria: Patients with specific immunocompromised status, defined as neutropenia with absolute neutrophil count less than 0.5×10^9^/L, current chemotherapy, or post-organ transplantation are excluded. Furthermore, pregnant patients, moribund patients and patients with a diagnosis that requires primary surgical intervention, or within 72 h after surgery are excluded. Patients are randomized using a minimization procedure [20]. The factors for minimization are imbalance in randomization result and study site. The randomization result is allocated at patient enrolment by a computer generated algorithm.

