
Statistical analyses for the primary study parameters:Antibiotics use. The percentage of patients that are prescribed antibiotics is compared between the PCT-guided group and control group using a Fisher’s exact test. Demographic parameters (age, sex, mortality), medical parameters (medication use, comorbidity, temperature, CRP and PCT measurements), hospital admission related parameters (hospital admittance, hospital length of stay, ICU admittance, ICU length of stay) are compared between the PCT-guided group and control group using Fisher’s exact tests for dichotomous variables, chi-square tests for categorical variables with more than two categories, t-tests for continuous variables that are normally distributed, and Kruskal-Wallis tests for continuous variables that are not normally distributed. A logistic regression analysis will be used to determine the influence of these parameters on the proportion of antibiotics prescriptions in the control group and the PCT-guided therapy group. To select the independent variables in this logistic regression model, we will use a stepwise backward approach in which only the independent variables are retained that have a significant effect using a significance level of 5 %; however, the variable group (PCT-guided group versus control group) will be included in the model irrespective of the results. In the event of missing values in possible confounding data, like intoxications and prescription drugs use, we will use multiple imputation. Both an intention to treat analysis and a per protocol analysis will be performed. Physician adherence to the PCT guidance will be determined.Safety. Significant differences between the PCT-guided group and control group in the composite safety endpoint are determined using a one-sided upper 95 % confidence limit for the difference in proportion between the PCT-guided group and the control group. This confidence interval will be calculated using the method of Agresti and Caffo [23]. Noninferiority of the intervention will be established if the 95 % confidence interval excludes 7.5 %, i.e. if PCT-guided prescription of antibiotics does not increase the rate of the composite endpoint by more than 7.5 percentage points. Differences in hospital length of stay will be assessed using the Kruskal-Wallis test.Accuracy of PCT and CRP. In all patients, the final diagnosis of the etiology of fever will be determined. Also, it will be determined if there is a bacterial infection. The variables “confirmed bacterial infection” and “suspected bacterial infection” will serve as gold standards for the evaluation of the accuracy of the biomarkers CRP and PCT. These will be determined retrospectively, using culture results and all diagnostic tests available. In all patients, both PCT and CRP levels will be available for statistical analysis. The ability to predict bacterial infection of both PCT and CRP will be evaluated using receiver operating characteristic curves, and the area under the curve will be calculated. In addition, logistic regression will be performed to analyze the effects of PCT and CRP levels on the probability of a bacterial infection. The independent variables in this analysis are age, sex, PCT, CRP, temperature, comorbidity, and other variables that have a *p* < 0.1 for the difference between groups. We will account for possible non-linear effects of age, PCT, CRP and temperature by using appropriate transformations of these variables.

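### Allocation is minimised by study site, but the named efficacy test, safety interval and efficacy covariates leave site out, which costs a little precision if site is prognostic

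*Protocol article*

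**What the plan says.** Under Inclusion and exclusion criteria, the protocol article describes allocation by minimisation: "The factors for minimization are imbalance in randomization result and study site". The first factor is the overall balance between arms, so site is the only patient-level factor balanced by design. Methods and design adds that the sites are of different kinds: "The study will be performed in both academic and non-academic teaching hospital settings".

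Under Sample size calculation and statistical analyses, the methods for the two between-arm comparisons are named:

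- Efficacy: "The percentage of patients that are prescribed antibiotics is compared between the PCT-guided group and control group using a Fisher’s exact test".
- Safety: an upper one-sided 95% limit for the difference in proportions, set against a 7.5-point margin. "This confidence interval will be calculated using the method of Agresti and Caffo".
- Efficacy regression: candidates are "Demographic parameters (age, sex, mortality), medical parameters (medication use, comorbidity, temperature, CRP and PCT measurements") and "hospital admission related parameters (hospital admittance, hospital length of stay, ICU admittance, ICU length of stay"). They are reduced by backward elimination at the 5% level, and treatment group is the only term protected from removal.

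The article describes no site-stratified or site-adjusted analysis of either endpoint.

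**The concern.** Balancing arms within site takes between-site variation out of the sampling variance of the arm difference. A pooled test or interval still includes it. If site predicts the outcome, the reported standard error is larger than the true one, so the interval is too wide and the test loses some power. Academic and non-academic hospitals may well differ in case mix, prescribing, ICU use and return visits.

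The safety comparison has the least to spare: it needs 244 per group, is planned at only 80% power, and leads to the total of 550. Any avoidable imprecision there uses up room under the 7.5-point margin.

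**Working it through.** **Inputs from the article.** Safety: 12.7% expected, margin 7.5 points, one-sided alpha 5%, power 80%, 244 per group. Efficacy: 73% versus 53%, two-sided alpha 5%, power 80%, 101 per group. Total 550, or 275 per group, with 10% dropout.

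**Assumptions.** The number of sites, their sizes and their rates are not given. I take two equal sites with arms exactly balanced within each, and vary the site rates.

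**Step 1: reproduce the stated sizes.** Safety: n = (1.645 + 0.842)² × 2 × 0.127 × 0.873 / 0.075² ≈ 244, as stated. Efficacy: the continuity-corrected formula gives 101, as stated, and exact Fisher power at 101 per group is 0.806. Neither calculation involves site.

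**Step 2: variance ratio.** With site weights w and site rates p_s averaging p, the ratio of the site-balanced to the pooled variance is Σ w·p_s(1 − p_s) / [p(1 − p)]. The pooled standard error is too large by a factor of 1/√ratio.

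Example, efficacy at 63% and 83%: (0.63 × 0.37 + 0.83 × 0.17)/2 = 0.1871; 0.73 × 0.27 = 0.1971; ratio 0.949; factor 1.026.

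| Endpoint | Site rates (%) | Variance ratio | Standard error too large by |
|---|---|---|---|
| Safety | 12.7 / 12.7 | 1.000 | 0% |
| Safety | 10.0 / 15.4 | 0.993 | 0.3% |
| Safety | 8.0 / 17.4 | 0.980 | 1.0% |
| Safety | 5.0 / 20.4 | 0.947 | 2.8% |
| Efficacy | 73 / 73 | 1.000 | 0% |
| Efficacy | 68 / 78 | 0.987 | 0.6% |
| Efficacy | 63 / 83 | 0.949 | 2.6% |
| Efficacy | 58 / 88 (extreme) | 0.886 | 6.3% |

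**Step 3: size on the safety scale.** With 12.7% in both arms and 244 per arm, the distance from estimate to upper limit is 1.645 × √(2 × 0.127 × 0.873 / 244) = 4.96 points. At 8.0/17.4 it becomes 4.96 × √0.980 = 4.91, a gain of 0.05 point against a 7.5-point margin. In patients, 244 × 0.980 ≈ 239 per arm would give the same precision.

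**Step 4: safety by simulation** (244 per arm, 100,000 runs per setting).

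| Site rates (%) | Type I error, Agresti-Caffo | Power, Agresti-Caffo | Power, stratified |
|---|---|---|---|
| 12.7 / 12.7 | 0.0515 | 0.802 | 0.802 |
| 10.0 / 15.4 | 0.0509 | 0.802 | 0.803 |
| 8.0 / 17.4 | 0.0506 | 0.803 | 0.808 |
| 5.0 / 20.4 | 0.0486 | 0.805 | 0.818 |

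The gain runs from nothing to 1.3 points. Only a very wide split such as 2.7/22.7 pulls the unadjusted type I error down to 0.0447, with power 0.813 against 0.834 stratified.

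**Step 5: efficacy.** At 73% versus 53%, exact Fisher power is 0.995 with 248 per group (275 less 10%) and 0.998 with 275, so stratifying cannot add anything material there. For an illustrative 10-point reduction, which the article does not plan for, simulated power at 275 per arm for Fisher against Cochran-Mantel-Haenszel is 0.683 against 0.716 with equal sites, 0.689 against 0.736 at 63/83, and 0.687 against 0.755 at 58/88. The 3.3-point gap with equal sites cannot be due to site. Only the widening of the gap beyond that is.

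**The case against.** The case for leaving the plan alone has several sound parts.

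- **The effect on safety is very small.** This stands. The unadjusted type I error is essentially nominal at all but very wide site differences, and half a point of power is at stake at 8.0/17.4.
- **Efficacy has ample power.** This also stands at the planned effect. Precision there matters only if the true reduction is much smaller.
- **The sizes are assumed.** True. Having academic and non-academic sites does not show that outcome rates differ, and unequal site sizes shrink the gain. For sites at 60% and 80%, the variance cut is 4.8% with equal sites but 2.8 to 3.5% with an 80/20 split.
- **The covariate list may not be closed.** The sentence on missing data mentions intoxications, which is not on the list, so site might be meant as a further candidate and a fuller document might say so. That weakens the regression part of the point. Even as a candidate, though, site could be dropped by backward elimination. The part about the named test and interval is unaffected: an analysis plan that stratified either one would depart from the method the article names.

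A reader might also infer that Fisher's actual size of about 4.0% is evidence of the mismatch. It is not: that size arises with no site effect at all. It is a property of the exact test, and the article's sample size was calculated for the same test.

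**Conclusion.** The point holds as a minor one. The trial balances on site, and the methods named for efficacy and safety do not use it. If site is prognostic, the unstratified standard error is too large by about 0 to 3% for moderate differences in site rates, by about 6% for extreme ones, and not at all if the rates are equal. These figures rest on two equal, exactly balanced sites with assumed rates.

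A reader might go further and infer that the results would be biased, that false claims of efficacy or noninferiority become more likely, that both primary analyses are materially conservative, or that the sample size is wrong. The documents support none of these. Any site effect runs towards caution, safety type I error stays near 5%, the stated 244 and 101 per group both reproduce, and efficacy is over 99% powered at the planned rates. What is lost is a little precision, chiefly in the safety comparison, which can be recovered at no cost in patients.

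**What to change.** Amend the analysis wording before the data are analysed:

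- **Safety:** take the site-stratified Mantel-Haenszel risk difference and compare its upper one-sided 95% limit with the 7.5-point margin.
- **Efficacy:** use a Cochran-Mantel-Haenszel test stratified by site, reported with the Mantel-Haenszel risk difference.
- **Logistic model:** keep site in the model alongside treatment group, exempt from backward elimination.
- **Small sites:** state in advance how very small sites are pooled, since the article does not give the number of sites.
- **Sensitivity analyses:** keep Fisher's test and the Agresti-Caffo interval.

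The cost is wording only. Site is already recorded because the allocation uses it, and neither the sample size nor data collection changes. Fixing the choice now also avoids choosing between adjusted and unadjusted results after they are seen.
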